## Abstract

**Background::**

Chinese herbal bath has long been used in the curative treatment of psoriasis vulgaris. However, there is no unified standard protocol for Chinese herbal bath. Many factors affect the curative effect of Chinese herbal bath, such as water temperature, bath concentration, and soaking time. Most studies involving Chinese herbal bath has described the bath generally, and few studies have investigated the factors that might contribute to the efficacy of Chinese herbal bath. Here we describe a protocol to evaluate the efficacy and safety of various bathwater temperatures and herbal concentrations on psoriasis vulgaris, and their effect on serum vascular endothelial growth factor (VEGF), tumor necrosis factor α (TNF-α), interleukin 23 (IL-23), and interleukin 17 (IL-17). These data could be useful for optimizing Chinese herbal bath treatments.

**Methods::**

In this randomized controlled trial, we planned to recruit 288 hospitalized atients with psoriasis vulgaris aged 18 to 65 years. All participants who meet the inclusion criteria will be randomly assigned to the observation group, the control group, or the basic treatment group. The observation group will be divided into 6 sub-groups according to water temperatures and bath concentrations, designated as observation groups 1 to 6. Thirty-six participants will be assigned to each group. The basic treatment group will be given co-qingdai capsule, po 2 g tid; compound glycyrrhizin tablet, po 75 mg tid; AA Skincare jojoba Oil, us.ext qd. The observation group will be given a Chinese herbal bath at the same time as the basic treatment. The control group will be given ozone hydrotherapy at the same time as the basic treatment. The entire treatment course will last for 2 weeks. The following parameters will be compared in each group, before and 2 weeks after treatment: the psoriasis area and severity index score (PASI), pruritus score, clinical efficacy, and dermatology life quality index score (DLQI); serum levels of serum VEGF, TNF-α, IL-23, and IL-17; and confocal laser scanning microscope images.

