**Conclusion::**

This study will evaluate the efficacy and safety of various Chinese herbal bath conditions (water temperatures and herbal concentrations) on the treatment of psoriasis vulgaris, which will provide an important reference for the operation of Chinese herbal bath.

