#### Sample size calculation

2.2.3

According to the calculation formula of sample size in clinical trials,^[7]^ the necessary estimated loss rate is 10%, and the total sample size is 288 cases, with 36 cases per group. There will be 36 participants assigned to each group, including 36 cases in the basic treatment group, 36 cases in the control group, and 36 cases in each of the 6 observation groups.

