### Data collection and management

2.7

All data will be analyzed according to the intention to treat principle. The missing value will be dealt with by carrying forward the most recent observation to the end point.

This study will use the IBM SPSS Statistics (version 22.0) software for data management and analysis. Professionally-trained dermatologists will collect all data. Members of the research team will perform the data collection and statistical analyses. Quantitative indicators will be expressed as mean ± standard deviation. If the sample is normally distributed and the variance is uniform, the *t* test will be performed: the paired sample *t* test will be used for intra-group comparison, and the independent sample *t* test will be used for inter-group comparison. If the variance is uneven, the approximate *t* test will be used. If the sample is not normally distributed, the rank-sum test (non-parametric) will be applied. The Chi-square test will be used for counting data. *P* values less than .05 will be considered as statistically significant.

The Chinese Ethics Committee of Registering Clinical Trials (Chengdu, China), which does not have any competing interests, will be responsible for monitoring the data. The Department of Science Research of the hospital at Chengdu University of TCM, which is independent of the investigators, will perform data audits in the trial.

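### Six bath arms are built from temperature and concentration, but section 2.7 names only two-sample tests and no analysis that estimates the two effects jointly, tests a trend or tests their interaction

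*Protocol article*

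**What the plan says.** The aim is about two factors. The abstract's background section sets out to "evaluate the efficacy and safety of various bathwater temperatures and herbal concentrations on psoriasis vulgaris", and its conclusion promises results on "various Chinese herbal bath conditions (water temperatures and herbal concentrations"). The design follows from this: "The observation group will be divided into 6 sub-groups according to water temperatures and bath concentrations". Section 2.2.3 gives the numbers: "the total sample size is 288 cases, with 36 cases per group", including "36 cases in each of the 6 observation groups".

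Section 2.7 then gives the analysis. For quantitative outcomes, which include the primary outcome PASI, the independent-sample t "test will be used for inter-group comparison". An approximate t test replaces it when variances differ, and a further fallback is stated: "If the sample is not normally distributed, the rank-sum test (non-parametric) will be applied". Counts get a chi-square test, and significance is at .05. The section does not list which groups are compared, and no model in it contains temperature or concentration as a factor. It also specifies intention to treat, with missing values filled by the last observation.

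**The concern.** Three quarters of the trial (216/288) is spent on arms that differ only in bath conditions, so the central question concerns the effects of temperature and concentration. A list of two-sample tests has no step that brings the arms together to answer it. It does not say how a temperature effect is to be summarised across concentrations, whether the response rises or falls over ordered levels, or whether the effect of one factor depends on the other. Optimising the bath depends on that last point.

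Section 2.7 does not defer the analysis to another document. It sets out a full decision path (normality, variance, fallback, significance level), and that path does not match the design. At stake are the precision of the trial's main answer and the ability to say whether the best temperature is the same at every concentration.

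**Working it through.** **Inputs from the protocol.** Eight arms of 36: 8 x 36 = 288, which agrees with section 2.2.3. Bath arms: 6 x 36 = 216. Significance level .05 (section 2.7), taken as two-sided. Loss 10% (section 2.2.3). The text gives no power, effect size or SD for the figure of 36, so its basis cannot be reproduced.

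**Assumptions.**
- The layout is a full crossing. With both factors varying and six arms, that can only be 2x3 or 3x2. The body of Table 1 and the figures were not available, so the levels could not be confirmed.
- There is no strong interaction.
- The true difference lies between 0.3 and 0.7 SD.
- 36 per arm are analysed, as intention to treat with carry-forward implies.

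**What the pairs of arms can show.** Six arms give 15 pairs. In a crossed 2x3, 3 pairs differ only in the two-level factor and 2 x 3 = 6 differ only in the three-level factor. The other 6 differ in both, so they separate neither effect.

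**Patients used.**
- One pair of arms: 36 + 36 = 72.
- Two levels of the three-level factor: each level has 2 arms, so 72 v 72 = 144. One pair uses 72/144, or half.
- Two-level factor: each level has 3 arms, so 108 v 108 = 216. One pair uses 72/216, or one third.

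**Standard error of a difference, in SD units: sqrt(2/n).**
- n = 36: 0.236
- n = 72: 0.167
- n = 108: 0.136

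**Power, normal approximation: Phi(d x sqrt(n/2) - 1.96).** For d = 0.5: 0.5 x sqrt(18) = 2.12, giving Phi(0.16) = 56%; 0.5 x sqrt(36) = 3.00, giving Phi(1.04) = 85%; 0.5 x sqrt(54) = 3.67, giving Phi(1.71) = 96%.

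| True difference | 36 v 36 | 72 v 72 | 108 v 108 |
|---|---|---|---|
| 0.3 SD | 25% | 44% | 60% |
| 0.4 SD | 40% | 67% | 84% |
| 0.5 SD | 56% | 85% | 96% |
| 0.6 SD | 72% | 95% | 99% |
| 0.7 SD | 84% | 99% | >99% |

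The difference detectable with 80% power, (1.96 + 0.84) x sqrt(2/n), is 0.66, 0.47 and 0.38 SD. Exact noncentral-t values agree within about 1.5 percentage points.

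**Sensitivity to loss.** With 32 evaluable per arm (36 x 0.9 = 32.4), power at 0.5 SD is 52%, 81% and 93%.

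**Interaction.** A difference of differences between four arms has standard error sqrt(4/36) = 0.333 SD, twice the 0.167 of the three-level marginal contrast.

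**Multiplicity.** If all 15 bath pairs were tested at .05 without adjustment, the chance of at least one false positive would be about 36% (20,000 simulated trials with no true differences). Section 2.7 does not say that all pairs will be tested.

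**The case against.** The strongest reply is that two-sample tests are not blind to the factors. In a crossed layout, a t test between two arms with the same concentration and different temperatures validly estimates the temperature effect at that concentration. If a factor has two levels, its marginal comparison (108 v 108) is itself an independent-sample t test. Nor does section 2.7 restrict its tests to single arms: sections 2.1 and 2.2.6 speak of three groups, so pooled comparisons are possible. Choosing the best of six conditions also needs comparisons of single arms, and marginal effects can mislead if the factors interact. Finally, six arms need not be crossed: temperatures could vary at one concentration and concentrations at one temperature.

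Much of this stands, and it rules out three readings that a reader might infer:
- That the plan compares only 36-patient arms. Section 2.7 does not say which groups enter the tests.
- That it can give no temperature or concentration effect. Simple effects are estimable from suitable pairs.
- That it throws away most of the available power. A single pair uses half of the informative patients for a three-level factor, so that description fits a two-level factor at most, and at 0.7 SD a single pair still has 84% power.

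What does not fall is the mismatch. A pooled bath group of 216 against ozone or basic treatment averages over both factors and says nothing about either. Pooling over one factor is not excluded, but it is not named, and it would not test the interaction. No reading of section 2.7 supplies a joint analysis or a trend test.

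**Conclusion.** The point holds in a limited form. The between-group analysis that the protocol states does not fit its two-factor aim: no named method estimates temperature and concentration effects jointly, tests a trend or tests their interaction. The trial would still be interpretable, but its main question lacks a matching analysis.

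The size of the loss is conditional. It rests on a crossed 2x3 layout, on interaction that is not strong, on an effect size that the protocol does not give, and on the effects being read from single pairs of arms. The gap in power is widest in the middle of the range: 29 or 40 percentage points at 0.5 SD, from the rounded figures above. If the layout is not crossed, these power figures do not apply, but the absence of a joint analysis remains.

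**What to change.** State in section 2.7 the factor levels and the layout that the analysis relies on.

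If the layout is crossed, analyse PASI in the six bath arms by two-way ANCOVA with temperature, concentration, their interaction and baseline PASI. Report the marginal effects (with a trend for the three-level factor), the interaction with its confidence interval, and the six adjusted arm means with intervals. If it is not crossed, use one baseline-adjusted linear model over the bath arms, with prespecified temperature and concentration contrasts.

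In either case, list the comparisons with ozone hydrotherapy and with basic treatment separately, say which contrasts are primary, and state how multiplicity is handled.

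The cost is analysis work and wording. PASI before treatment and in the second week is already collected, and arms and recruitment do not change. If marginal contrasts become primary, section 2.2.3 should justify 36 per arm for them. The downside is that marginal effects average over the other factor. With a standard error of about 0.33 SD for a difference of differences, a non-significant interaction is weak evidence that there is none, so its interval and the six arm means must stand beside the marginal effects.

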**Conclusion::**

This study will evaluate the efficacy and safety of various Chinese herbal bath conditions (water temperatures and herbal concentrations) on the treatment of psoriasis vulgaris, which will provide an important reference for the operation of Chinese herbal bath.

**Trial registration number::**

ChiCTR1900027468

## Introduction

1

Psoriasis affects about 2% of the global population, and psoriasis vulgaris accounts for about to 90% of the incidence of psoriasis.^[1]^ Though the exact etiology and pathogenesis of psoriasis are not completely clear, there is a broad consensus that the immune system is involved in the pathogenesis of psoriasis. Through whole-genome analysis, most genes associated with psoriasis are immune-related. Psoriasis inflammation is mostly driven by innate and acquired immunity disorders.^[2]^ By promoting angiogenesis and the release of pro-inflammatory cytokines and chemokines, vascular endothelial growth factor (VEGF), tumor necrosis factor a (TNF-а), interleukin 23 (IL-23), and interleukin IL-17(IL-17) play important roles in the pathogenesis of psoriasis.^[3,4]^ Because of its complex pathogenesis, at present, psoriasis cannot be cured completely. Psoriasis treatments mostly aim to control and stabilize the disease, decrease the development process, reduce clinical symptoms (erythema, scale, plaque thickening, and pruritus), reduce short- and long-term adverse reactions, control psoriasis-related complications, and improve the patients’ quality of life.^[5]^

Traditional Chinese Medicine (TCM) has unique advantages in the treatment of psoriasis, and increasing incorporation of TCM into clinics has greatly improved psoriasis outcomes.^[6]^ However, there is as yet no unified standard protocol for Chinese herbal bath, and few studies have investigated the factors affecting the efficacy of Chinese herbal bath, such as water temperatures, bath concentrations, and soaking time.

To address this, here we plan to use Chinese herbal bath to treat psoriasis vulgaris patients, for testing multiple water temperatures and herbal concentrations. Based on the study outcomes, we will assess the severity of the psoriasis vulgaris and serum VEGF, TNF-α, IL-17, and IL-23 levels. These data will help to optimize Chinese herbal bath protocols and provide insights into the therapeutic mechanisms of Chinese herbal bath in the treatment of psoriasis.

## Methods

2

### Study design

2.1

The study has been planned as a single-center, parallel-group, randomized controlled trial (RCT). The Chinese Ethics Committee of Registering Clinical Trials has approved this study. Patients meeting the inclusion criteria will first be screened. All participants will sign informed consent forms, and they will be randomly assigned to the observation group, the control group, or the basic treatment group. Randomization will be performed through IBM SPSS Statistics 22.0 software's random number generator. Figure 1 presents the schedule of enrolment, interventions, and assessments. Figure 2 shows a flow chart of the study.

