#### Inclusion criteria

2.2.1

The inclusion criteria are: inpatients; patients corresponding to diagnosis standards psoriasis vulgaris with Western Medicine; patients corresponding to diagnosis standards psoriasis vulgaris with the blood-heat syndrome of Traditional Chinese Medicine; patients corresponding to the progressive stage of psoriasis vulgaris; patients diagnosed with psoriasis vulgaris between 18 and 65 years old, regardless of gender and course of the disease; patients that have provided informed consent, and voluntarily accept and cooperate with treatment, examination, and observation.

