#### Randomization and blinding

2.2.4

Randomized grouping will be done using IBM SPSS statistics (version 22.0) software's random number generator.

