#### Participants recruitment

2.2.7

The participants will be recruited from the Hospital of Chengdu University of Traditional Chinese Medicine and Chengdu Yinkang Psoriasis Hospital by an open recruitment method. Participants will be screened according to the inclusion and exclusion criteria. The recruiting members will be [name], associate chief physician [name], associate chief physician [name], attending physician [name], and attending physician [name].

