#### The observation group treatment

2.3.4

The observation group will be given Chinese herbal bath at the same time as the basic treatment.

The Chinese herbal bath prescription will be composed of: phellodendron (30 g), rhubarb (15 g), sophora flavescens (30 g), purslane (30 g), fructus kochiae scopariae (30 g), glycyrrhiza (30 g), mirabilite (20 g), alumen (10 g), and borneol (3 g).

All of the above Chinese herbs are provided by the Chinese medicine pharmacy of Chengdu Yinkang Psoriasis Hospital and decocted by the boiling machine of Chengdu Yinkang Psoriasis Hospital. According to the methods of the decoctum preparation and the standardization of decoction preparation in “Treatise on Exogenous Febrile Diseases,”^[10]^ and the management standard of Chinese medicine decoction room,^[11]^ the decoction amount is 1 L per dose. Table 1 shows Chinese medicine liquid and diluent of different concentrations.

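### The trial is called single-center but recruits from two hospitals, and neither the described randomisation nor the named tests take account of hospital: a contradiction to reconcile and a modest loss of precision

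*Protocol article*

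**What the plan says.** **Number of centers.** Section 2.1 (Study design): "The study has been planned as a single-center, parallel-group, randomized controlled trial (RCT". Section 2.2.7 (Participants recruitment): "The participants will be recruited from the Hospital of Chengdu University of Traditional Chinese Medicine and Chengdu Yinkang Psoriasis Hospital". Section 2.2.1 limits entry to hospitalised patients: "The inclusion criteria are: inpatients". The article does not say whether patients found at one hospital are admitted, bathed or scored at the other.

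**Preparation of the bath.** Section 2.3.4 has the herbs supplied by one of the two hospitals and "decocted by the boiling machine of Chengdu Yinkang Psoriasis Hospital". Six of the eight arms depend on this decoction.

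**Randomisation.** Section 2.2.4: "Randomized grouping will be done using IBM SPSS statistics (version 22.0", using its random number generator. Section 2.2.5 describes one allocation form in three copies. Neither section, nor 2.1, mentions hospital. Section 2.2.6 rules out blinding.

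**Size.** Section 2.2.3: "the total sample size is 288 cases, with 36 cases per group".

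**Analysis.** Section 2.7 names the independent-sample t test for comparisons between groups, an approximate t test if variances differ, a rank-sum test if the data are not normal, and the chi-square test for counts. As named, none of them includes hospital.

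**The concern.** Whether a trial has one center or two is a basic design statement, and the article gives two answers that do not fit together. An analysis plan would not settle this.

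The statistical methods follow the single-center answer. If patients are in fact admitted and treated in two places, hospital is a plausible source of variation in PASI. One institution is a university hospital of traditional medicine and the other a specialist psoriasis hospital, so case mix may differ. PASI is rated by clinicians without blinding, so rating habits may differ too.

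An unstratified list lets the hospital mix vary by chance across eight arms of 36. An unadjusted test then leaves the hospital variance in the error term. What is at stake is the precision of comparisons among six bath conditions and two comparators.

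**Working it through.** **The plan's own figure.** Eight arms of 36 give 8 × 36 = 288, as stated. With the 10% loss rate in section 2.2.3, 32 / 0.90 = 35.6, which rounds up to 36. So 36 fits 32 evaluable patients per arm, although the article does not say this. It gives no effect size, SD or power, so 36 cannot be derived further. I use 36 per arm because section 2.7 analyses everyone by intention to treat and carries the last observation forward.

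**Assumptions.** The documents give neither the share p of patients from one hospital nor the PASI difference h between hospitals. I take p from 0.5 to 0.9 and h as 0.5 or 1.0 within-hospital SD. The test is taken as two-sided at 0.05.

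**Step 1: chance imbalance without stratification.** The SD of the difference in hospital share between two given arms is √(2p(1−p)/36). At 50:50 this is √(2 × 0.25/36) = 0.118. The probabilities come from 40,000 simulated random allocations of 288 patients to eight arms of 36.

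| Split | SD of difference | Two given arms differ by ≥10 points | by ≥20 points | Largest gap among eight arms ≥20 points |
|---|---|---|---|---|
| 50:50 | 0.118 | 41% | 8% | 64% |
| 70:30 | 0.108 | 37% | 5% | 53% |
| 80:20 | 0.094 | 30% | 3% | 34% |
| 90:10 | 0.071 | 17% | 0.3% | 5% |

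**Step 2: added variance.** Leaving hospital out raises the outcome variance from 1 to 1 + h²p(1−p).
- h = 0.5: 0.25 × 0.25 = 0.0625 at 50:50, so about 6% more variance and √1.0625 = 1.031, or 3% on the standard error. At 80:20 it is 0.25 × 0.16 = 0.04.
- h = 1.0: 0.25 at 50:50 and 0.16 at 80:20.

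The same result follows from the imbalance. For a given pair of arms at 50:50 and h = 0.5, the hospital contribution has SD 0.118 × 0.5 = 0.059, against a standard error of √(2/36) = 0.236. The ratio of variances is (0.059/0.236)² ≈ 0.06.

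**Step 3: type I error and power of the unadjusted t test.** With 36 per arm, 80% power corresponds to a difference of (1.960 + 0.842) × √(2/36) = 0.66 SD, so I use 0.66 as the reference effect. There are 20,000 simulated two-arm comparisons per cell.

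| Hospital effect | Split | Type I error | Power at 0.66 SD |
|---|---|---|---|
| none | – | – | 78.9% |
| 0.5 SD | 50:50 | 4.7% | 76.2% |
| 0.5 SD | 80:20 | 4.6% | 76.5% |
| 1.0 SD | 50:50 | 4.9% | 69.5% |
| 1.0 SD | 80:20 | 4.8% | 72.1% |

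Type I error does not rise above 5%. The power loss is about 2 to 9 points.

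**The case against.** **Hospital is not confounded with arm.** A reader might infer confounding from the sight of two hospitals and an unstratified list. The documents do not support that. Patients are assigned individually at random, so hospital has no systematic link to arm, and the standard error of the t test already reflects the chance imbalance. Systematic confounding would require some arms to be delivered at one hospital only. Decoction at a single hospital raises the question, but no section says it happens. This objection stands in full.

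**The extreme-arm figure is a worst case.** At 50:50 the expected gap in hospital share between the highest and lowest of eight arms is about 0.24. Multiplied by 0.5 SD, that gives about 0.12 SD, which a reader might take as a bias. It compares the two arms that happen to differ most on hospital share, under the split that maximises imbalance, and it is not a planned contrast. It should not be quoted as the size of the problem.

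**Two-site treatment is an inference.** Section 2.2.7 says where patients are recruited, not where they are treated. Decoction at one hospital would fit a single treatment site with two recruiting sources. Section 2.3.5 gives one bathing procedure, and no section says that delivery or rating differs by hospital. This stands too, and it is why the request is to reconcile the sections and not simply to relabel the trial as two-center.

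**Silence on stratification.** This is a condensed article, and stratification may be described in a fuller document. That weakens the point about the list. It weakens the point about analysis less, because section 2.7 does name the tests and they are unadjusted. Unadjusted tests are valid here; they are less precise than they could be.

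**Conclusion.** The contradiction between sections 2.1 and 2.2.7 is certain and needs to be resolved in the text. The statistical consequence is conditional and moderate. If the hospitals differ in PASI, the design and tests as described lose precision, with no bias and no inflation of type I error.

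The 6% rise in variance assumes a 0.5 SD hospital effect and an even split; at 80:20 the rise is 4%. The loss of 2 to 9 points of power covers assumed effects of 0.5 to 1.0 SD at splits of 50:50 and 80:20. If nearly all patients come from one hospital, or the hospitals hardly differ, the loss is smaller still. The documents do not show which of these cases applies.

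**What to change.** 1. Reconcile sections 2.1 and 2.2.7: state how many centers there are and where patients are admitted, bathed and scored.
2. Stratify the eight-arm list by hospital, or by recruiting source if all patients are treated at one site. Because the trial is unblinded, keep the block sizes concealed and vary them at random, so that late assignments in a block cannot be guessed. With eight equal arms, block sizes must be multiples of eight.
3. Replace the unadjusted between-group t test for PASI with a linear model containing arm, hospital and baseline PASI. Baseline PASI is already recorded under section 2.3.7.

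Steps 2 and 3 belong together. In the same simulations, a stratified list analysed with the unadjusted t test had type I error between 2.8% and 4.7%, so part of the gain from stratifying would be wasted.

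The cost is two randomisation lists instead of one, possibly arm sizes slightly off 36 if the last block in a hospital is incomplete, and a model in place of the t test. No extra patients or measurements are needed.
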